## 5.3 RANDOMIZATION AND STRATIFICATION

Stratified block assignment with the number of weeks after birth (7 to 10 weeks, 11 to 13 weeks) as the factor in the order of registration is performed and participants are randomly assigned to the “aggressive intervention group” or “conventional treatment group” in a ratio of 1:1.

Justification for stratification

At an early onset, atopic dermatitis tends to be severe, so the number of weeks after birth was assigned as an adjustment factor.

## 5.4 BLINDING

Participants, parents, and investigators who treat participants with AD are not blinded to the study intervention. The physicians who perform OFC and examine the skin are blinded to the group allocations. Those who are blinded to the study intervention are required to meet the following criteria.

1. Blinded physicians are not the physicians who treat participants in the PACI Study.
2. Blinded physicians do not look at documents and all other information about the study intervention.

## 5.5 PATIENT BACKGROUND SURVEY AND START OF STUDY TREATMENT

Study physicians examine the participants’ background at study entry. They will prescribe study drugs for participants and start to treat them.

## 5.6 STUDY INTERVENTION

5.6.1 STUDY INTERVENTION FOR BOTH GROUPS

Proxies (parents or legal guardians) of the participants will obtain skin care education and nutritional education for participants on the day of study registration.

**Skin care education**

Skin care education is performed based on the Guidelines for the Management of Atopic Dermatitis (2016) (1). Proxies (parents or legal guardians) of the participants watch an instructional video on how to wash the body. They are given an information sheet.

**Education for applying ointments**

In the aggressive treatment group and the conventional treatment group, the presence of eczema, its severity, and the topical medicines that are applied according to the sites and duration of application are defined as follows (5.6.1, 5.6.2). The applied amount is 1 FTU. The study physician distributes instructions for applying topical medicines and determining the severity of skin rash to the proxies (parents or legal guardians) or their families at the time of registration so that participants can be treated with study medications at home. The study physician prescribes the topical medicines to be used, and the proxy (parents or legal guardians) or their families conduct the study treatment using the prescribed topical medicines. The proxy (parents or legal guardians) or their families do not discard the topical medicines that are not used, and bring all containers and all remaining topical medicines at the time of visit. Study physicians and/or staff instruct the proxies (parents or legal guardians) or their families to record the application situation of topical medications and severity of the skin rash in the treatment diary, and confirm the log of the treatment diary for each visit.

**Nutritional education**

Study physicians provide information about nutrition at the entry. It is recommended to introduce solid food to infants at 4–5 months of age. Breastfeeding is encouraged to continue until at least 6 months of age. Mothers who are breastfeeding are not restricted from ingesting hen’s egg. Participants are not permitted to eat hen’s egg until the oral food challenge test at the age of 28 weeks is complete. The nutritional intake status of participants is checked at the visit. In this study, unapproved medications and medical devices are not used.

5.6.2 STUDY TOPICAL MEDICINES

Participants apply the emollients and TCSs described below as study drugs.

Emollients: Heparinoid cream (Hirudoid^®^ Soft ointment)

TCSs: Alclometasone dipropionate (Almeta^®^), betamethasone valerate (Rinderon^®^-V), and mometasone furoate (Fulumeta^®^)

Study physicians obtain the most recent information about the study medicines (Hirudoid^®^ Soft ointment, Almeta^®^, Rinderon^®^-V, and Fulumeta^®^) from their package inserts.

5.6.3 Aggressive intervention group: Early aggressive treatments with topical corticosteroids

(Proactive method)

Basic whole-body treatment

Participants will be followed as described below and administered basic whole-body treatment, except for scalp.

Emollients

|  | Whole body except scalp |
| --- | --- |
| Registration day (Day 0) of the study  to 28 weeks of age | Hirudoid^®^ Soft ointment  every day  twice a day |

Topical corticosteroids

|  | Face | Body except scalp and face |
| --- | --- | --- |
| Registration day (Day 0) to Day 14 of the study | Almeta^®^ ointment  every day  twice a day | Rinderon^®^-V ointment  every day  twice a day |
| Day 15 of the study  to 28 weeks of age | Almeta^®^ ointment  two days per week  twice a day | Rinderon^®^-V ointment  two days per week  twice a day |

If participants do not have remission of atopic dermatitis on the 14th day (visit 2) after registration, daily administration of topical corticosteroid steroids is continued until day 28 (visit 3) after registration.

Additional skin rash treatment

Participants are to apply TCSs as additional treatment as described below:

| Face | Body except scalp and face | Scalp |
| --- | --- | --- |
| Day 15 of the study  to 28 weeks of age | Day 15 of the study  to 28 weeks of age | Day 15 of the study  to 28 weeks of age |
| Almeta^®^ ointment  every day until rash remission  , twice a day | Rinderon^®^-V ointment  every day until rash remission, twice a day | Rinderon^®^-V lotion  every day until rash remission  , twice a day |

Note:

When skin rash recurs, participants should re-apply TCSs on their body daily until they obtain remission of the skin rash.

If participants do not have remission from the skin rash by applying Rinderon^®^-V ointment for 7 days, they are permitted to use Fulumeta^®^ ointment.

When ointment is removed by washing or wiping, it can be re-applied.

Participants should frequently apply ointment to the area around the mouth to keep the skin around their lips covered with ointment.

5.6.4 Conventional treatment group: Standard treatment based on the Guidelines for the Management of Atopic Dermatitis (2016) (1) (Step-up reactive method)

Basic whole-body treatment

Participants will be followed as described below and administered basic whole-body treatment, except for scalp.

|  | Whole body except scalp |
| --- | --- |
| Registration day (Day 0) of the study  to 28 weeks of age | Hirudoid^®^ Soft ointment  Every day  twice a day |

Additional skin rash treatment

Participants are to apply TCSs as additional treatment as described below:

| Area | Face | | Body except scalp and face | | | Scalp |
| --- | --- | --- | --- | --- | --- | --- |
| Severity of skin rash | Less mild | Mild, moderate, and severe | Less mild | Mild and moderate | Severe | Any severity |
| Registration day (Day 0) of the study  to 28 weeks of age | Without additional treatment | Almeta^®^ ointment  every day until rash remission  once a day | Without additional treatment | Almeta^®^ ointment every day until rash remission  once a day | Rinderon^®^-V  ointment  every day until rash remission  once a day | Rinderon^®^-V valerate lotion until rash remission  once a day |

Note:

When skin rash recurs, participants should re-apply TCSs on their body daily until they obtain remission of the skin rash.

If participants do not have remission from the skin rash by applying Rinderon^®^-V for 7 days, they are permitted to use mometasone (Fulumeta^®^).

When ointment is removed by washing or wiping, it can be re-applied.

If study physicians judge participants do not obtain remission to AD 8 weeks after the entry, they can change the treatment to aggressive intervention treatment, which is treated as a deviation.

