**IgE-mediated hen’s egg allergy proven by the oral food challenge test (OFC)**

A positive open hen’s egg challenge test at the age of 28 weeks is assessed by a blinded physician (see 6.2). Following the PRRACTALL criteria in Table 6 (65), the challenge tests are scored as positive if participants meet any of the three criteria below within 2 hours after last ingesting hen’s egg:

1. One or more [A] scoring areas
2. Three or more [B] scoring areas
3. Persistence of one or more [B] scoring areas

Table 6. Scoring the challenge outcome (PRRACTALL criteria) (65)

| Ⅰ.  Skin | A. Erythematous rash: % area involved (see body surface area diagram), using rule of five.  0 = Absent  1 = Mild, few areas of faint erythema / 1-3 spots, 5-10％  2 = Moderate areas of erythema / >10%, ≤50%  3 = Severe generalized marked erythema / >50%  Figure 4. Rule of five  [figure not shown] | |
| --- | --- | --- |
|  | B. Pruritus | 0 = Absent |
|  |  | 1 = Mild, occasional scratching |
|  |  | 2 = Moderate: scratching continuously for >2 minutes at a time |
|  |  | 3 = Severe: hard continuous scratching, excoriations [B] |
|  | C. Urticaria / angioedema | 0 = Absent |
|  |  | 1 = Mild: less than 3 hives, or mild lip edema [B] |
|  |  | 2 = Moderate: more than 3 and less than 10 hives, or significant lip or face edema [A] |
|  |  | 3 = Severe: generalized involvement [A] |
|  | D. Rash | 0 = Absent |
|  |  | 1 = Mild: few areas of faint erythema |
|  |  | 2 = Moderate: areas of erythema [B] |
|  |  | 3 = Severe: generalized marked erythema (>50%) [A] |
| Ⅱ. Upper respiratory | A. Sneezing/ Itching | 0 = Absent |
|  |  | 1 = Mild: rare bursts, occasional sniffling |
|  |  | 2 = Moderate: bursts <10, intermittent rubbing of nose and/or eyes or frequent sniffling [B] |
|  |  | 3 = Severe: continuous rubbing of nose and/or eyes, periocular swelling and/or long bursts of sneezing, persistent rhinorrhea [A] |
| Ⅲ.  Lower respiratory | A. Wheezing | 0 = Absent |
|  |  | 1 = Mild: expiratory wheezing on auscultation [A] |
|  |  | 2 = Moderate: inspiratory and expiratory wheezing [A] |
|  |  | 3 = Severe: use of accessory muscles, audible wheezing [A] |
|  | B. Laryngeal | 0 = Absent |
|  |  | 1 = Mild: >3 discrete episodes of throat clearing or cough, or persistent throat tightness/pain [B] |
|  |  | 2 = Moderate: hoarseness, frequent dry cough [A] |
|  |  | 3 = Severe: stridor [A] |
| Ⅳ.  Gastrointestinal | A. Subjective Complaints | 0 = Absent |

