5.1.3 ANTICIPATED PARTICIPANTS AND STUDY DURATION

Anticipated number of participants: N=650 (aggressive intervention group: n=325 and conventional treatment group: n=325)

Duration of the study registration: 2 years from the day of IRB approval

Duration of the study intervention: 3 years after IRB approval

The study duration will be from study entry until completion of primary outcome assessment or until study termination. During the study duration, study treatment is continued unless the study treatment discontinuance criteria are satisfied. The study duration will be postponed under IRB approval if the study is not completed as scheduled.

Justification for the anticipated number of participants

Palmer *et al.* performed a double-blind, randomized controlled trial for infants with AD to test whether or not one-sixth of a raw whole egg taken every day can prevent development of IgE-mediated egg allergy. The infants were allocated to receive 1 teaspoon of pasteurized raw whole egg powder (n=49) or rice powder (n=37) daily from 4 to 8 months of age (67). A high proportion (31% [15/49]) of infants randomized to receive egg had an allergic reaction to the egg powder and 20% (10/49) had a reaction at the first ingestion of egg powder (one-sixth of a raw whole egg) at 4 months of age. When the control group participants received half of a raw egg provocation test at 12 months, 51% (18/35) were diagnosed with IgE-mediated egg allergy. These data suggested that prevalence of egg allergy in infancy is likely to depend on the provocation dose of egg and the preparation of egg such as heated or raw, and also on age and race of the participant. Therefore, we estimate that at least 30% of the participants in the conventional treatment group in this study will be diagnosed with IgE-mediated hen’s egg allergy using an oral food challenge test at the age of 28 weeks. However, the prevalence of IgE-mediated hen’s egg allergy among infants treated with early aggressive intervention for AD has never been reported. In Japan, it is common that infants at the age of 28 weeks do not eat hen’s eggs, and the prevalence of hen’s egg allergy at the age of 28 weeks in Japan is unclear. We consider a clinically effective prevalence of infants with early aggressive intervention for AD to be 20%. As discussed above, the calculated sample size is 614. Taking into consideration that the rate of drop out is about 5%, we determined the anticipated number to be 650.

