## 5.9 STUDY COMPLETION AND DISCONTINUATION

5.9.1 STUDY COMPLETION

The study is complete when the oral food challenge tests at 28 weeks of age are performed. When primary outcome evaluation is finished, study treatment for a participant is completed and study physicians observe, conduct tests, and evaluate the participant at the time of the study completion.

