Food challenge test (hen’s egg): open method investigated by blinded physician at the age of 28 weeks. Pasteurized low egg powder 2.6 g (whole egg 10.4 g, egg protein 1.2 g) is given. Participants eat 0.1–0.5–2 g of the pasteurized egg powder every 40 minutes.

History of IgE-mediated FA by interview, history of wheeze by interview

Serum test: total IgE antibodies titer in serum; egg white titer; ovomucoid, milk, soy, wheat, peanut and Ara h2-specific IgE antibody levels in serum; egg white titer; ovomucoid, milk, soy, wheat, peanut and Ara h2-specific IgG4 antibody levels in serum

Severity of AD: POEM, EASI by blinded physician

AD disease-free days, Prescription volume/remaining amount/days used of emollients and TCS used including rescue medication used

Salivary cortisol, concomitant medication/treatment, adverse events

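### Only the aggressive arm is told to keep the skin around the lips covered with ointment, and no common perioral skin condition is set for the egg challenge, so challenges decided by local skin signs could differ by arm for reasons other than allergy

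*Protocol*

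**What the plan says.** **Treatment notes.** In Section 5.6.3 the aggressive arm is told: "Participants should frequently apply ointment to the area around the mouth to keep the skin around their lips covered with ointment". The note names no product and gives no end date. The arm also has the note "When ointment is removed by washing or wiping, it can be re-applied". Section 5.6.4 repeats that re-application note for the conventional arm but has nothing about the mouth or lips. The synopsis (Section 0.6) carries the perioral note for neither arm.

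**Duration of treatment.** Section 5.1.3 runs the study duration to completion of the primary outcome assessment and adds: "During the study duration, study treatment is continued unless the study treatment discontinuance criteria are satisfied". Section 5.9.1 says: "When primary outcome evaluation is finished, study treatment for a participant is completed".

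**Challenge.** Section 6.2 describes the hen's egg challenge as an "open method investigated by blinded physician at the age of 28 weeks", fed in steps: "Participants eat 0.1–0.5–2 g of the pasteurized egg powder every 40 minutes". It says nothing about ointment or skin preparation around the mouth.

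**Scoring.** Under Section 3 and Table 6, a challenge is positive with one [A] area, with three [B] areas, or with one [B] area that persists, within 2 hours of the last dose. The urticaria/angioedema item includes "1 = Mild: less than 3 hives, or mild lip edema [B" and "2 = Moderate: more than 3 and less than 10 hives, or significant lip or face edema [A", where the closing letter is the scoring category. Moderate rash is a [B]. No item distinguishes skin touched by egg from other skin.

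**The concern.** The primary endpoint is read from a scoring table in which skin signs alone can decide the result. Infants of about 28 weeks who are fed egg powder in three steps will foreseeably get some of it on the skin around the mouth. If that skin is more reliably under ointment in one arm, a local contact sign may be less likely to appear there, whether or not the infant is allergic. That would be a difference in how the endpoint is measured, not in what the treatment prevents, and it would lower the positive rate in the aggressive arm, as the hypothesis predicts.

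The second issue is blinding. Parents and treating physicians know the allocation and the challenge is open, so the blinded challenge physician (Section 5.4) is the main safeguard. Ointment kept around the mouth in one arm by instruction lies on an area that this physician has to score. Section 5.4 bars access to documents and information about the intervention, but does not deal with what can be seen on the infant.

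**Working it through.** The point turns on reading the sections together. It rests on no calculated figure in the plan.

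1. **Is the instruction confined to one arm?** Yes. The two sets of notes run in parallel: recurrence of rash, step-up after 7 days and re-application appear in both. Perioral cover appears only in Section 5.6.3.

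2. **Is it in force on challenge day?** By inference, yes. Treatment continues until the primary outcome evaluation is finished (Sections 5.1.3 and 5.9.1), and that evaluation is the challenge. No section pauses the note, asks for ointment to be removed, or prescribes a common preparation. No section expressly orders ointment during the feed either.

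3. **Can local signs decide the endpoint?** The Table 6 skin items give:

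| Sign | Category | Positive on its own? |
|---|---|---|
| Erythematous rash by area (I.A), any grade | none | no |
| Pruritus, mild or moderate | none | no |
| Pruritus, severe | [B] | only if it persists |
| Fewer than 3 hives, or mild lip edema | [B] | only if it persists |
| More than 3 and fewer than 10 hives, or significant lip or face edema | [A] | yes |
| Rash, mild (faint erythema) | none | no |
| Rash, moderate | [B] | only if it persists |
| Generalized urticaria or generalized marked rash | [A] | yes, but not a local contact sign |

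The exposed group is therefore limited to challenges decided by local hives, moderate rash, or lip or face edema. Faint redness around the mouth does not score, and ointment would not plausibly prevent systemic signs.

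4. **How large is the contrast between arms?** Partial. Both arms apply Hirudoid Soft ointment twice daily to the whole body except the scalp, which includes the face (Sections 5.6.3 and 5.6.4). Both may re-apply after washing or wiping, and both may use petrolatum (Section 5.7). Conventional-arm infants with a facial rash of at least mild severity also apply ointment to the face. What differs is the instruction to keep the lip area covered.

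5. **Can the effect be sized?** No. It would need the share of challenges decided only by contact-confined signs and the fraction of those that ointment suppresses. The protocol gives neither. The planned 30% in the conventional arm (Section 5.1.3) does not help: it is a rate of allergy as diagnosed by the challenge, so it may already include any contact-driven positives and cannot be treated as the rate of true allergy.

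**The case against.** The strongest reply is that the note is home care. Section 5.6.1 explains that the application instructions are handed out so that treatment can be given at home, and the perioral note sits among notes on recurrence, washing and wiping. It may also be a deliberate part of the intervention, since the protocol's rationale is to prevent sensitization through the skin. On that view it says nothing about a supervised feed in a clinic.

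This stands in part. A reader might infer that the protocol orders ointment during the challenge; it does not. A reader might also infer shielded lips in one arm and bare lips in the other; the facial emollient, the re-application note and the permitted petrolatum rule that out. For the same reason ointment on the face does not by itself identify the arm, so the documents do not support saying that blinding is lost.

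What remains is that treatment formally runs through the challenge, and the challenge procedure does not say how the mouth area is to be presented. Caregivers who follow the Section 5.6.3 note may well bring the infant with the lip area covered. Occasional or optional cover in the other arm is not the same as an instruction to keep it covered. Accepting perioral cover as part of the intervention until the challenge does not require it to differ while the endpoint is being read.

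It can also be said that the sensitivity analysis belongs in the SAP, which is not shown. That is fair, but such an analysis needs a data item that the protocol's challenge procedure does not mention.

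**Conclusion.** The point holds as a possible arm-linked difference in how the only primary endpoint is measured, with a possible partial cue to the blinded physician. It rests on three assumptions: that caregivers follow the note on the day of the challenge, that egg reaches the perioral skin during feeding, and that ointment reduces local contact signs there. Its direction favours the aggressive arm.

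Its size is unknown. A reader might be tempted to assume a rate of contact-only positives and turn it into percentage points of the planned 30% versus 20% contrast, or into an inflated error rate. Any such number would be wholly the product of the assumption, so none is given. The point deserves correction because it touches the primary endpoint, is cheap to remove beforehand, and cannot be resolved afterwards if the site of the signs was not recorded. It does not show that the trial's result would be wrong.

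**What to change.** - **Reconcile Sections 5.6.3, 5.6.4, 5.9.1 and 6.2** so that perioral skin is in the same stated condition in both arms during the challenge and its 2-hour observation, and is set before the blinded physician assesses the infant. Which condition is chosen is a clinical decision for the investigators; for the comparison it matters only that it is the same.
- **Add one item to the challenge form and eCRF**: were the scoring signs confined to skin touched by egg?
- **Add one sensitivity analysis of the primary endpoint**, here or in the SAP, that does not count such isolated signs as positive. The primary definition stays as it is.

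The cost is a short addition to the challenge procedure, one extra eCRF item, one additional analysis, and a small departure from usual home care on the day of the challenge.

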## 5.7 PERMITTED CONCOMITANT TREATMENT

Permitted concomitant treatments are described below. Investigators assess the concomitant treatment every study visit.

1. Inhaled, nasal, ocular, and ear drop steroids
2. Petrolatum (white petrolatum: Propeto^®^) ointment
3. Treatment for skin diseases except for AD

Zinc oxide ointment, dimethylisopropylazulene ointment (e.g., Azunol^®^ ointment 0.033%), antibiotic ointment (e.g., nadifloxacin ointment: Acuatim^®^ ointment 1%), antivirus ointment (e.g., acyclovir ointment: Zovirax^®^ ointment 5%), antifungal ointment (e.g., allylamine antifungal ointment: Lamisil^®^ cream 1%), keratolytic and dry skin ointment (e.g., urea ointment: Pastaron^®^ cream 10%), ointment-steroid combinations (e.g., killed bacteria-hydrocortisone combinations: Eksalb^®^; chloramphenicol fradiomycin sulfate ointment: Chlomy^®^-p ointment)

1. Laser therapy for pigmented nevi, angioma, and so forth.

## 5.8 NON-PERMITTED CONCOMITANT TREATMENT

Concomitant treatments described below are not permitted because of their effect on the efficacy of the study.

1. TCSs except study medications
2. NSAID topical ointment (e.g., Ibuprofen piconol: Staderm^®^ ointment)
3. Systemic (oral or intravenous) steroids
4. Immunosuppressive medications except topical/oral/intravenous steroids (cyclosporine, tacrolimus, and so forth)
5. Biologics except vaccinations (Infliximab, Etanercept, Tocilizumab, and so forth)
6. Immunoglobulin

